# A multi-centre, double-blind, 12-week, randomized, placebo-controlled trial to assess the efficacy of adjunctive N-Acetylcysteine for treatment-resistant PTSD: a study protocol

**DOI:** 10.1186/s12888-020-02793-9

**Published:** 2020-08-06

**Keywords:** Clinical trial protocol, N-acetyl cysteine, Post-traumatic stress disorder, N-acetyl cysteine, Adjunctive therapy, Randomised clinical trial, Oxidative stress, Biomarker

## Abstract

**Background:**

Most patients with Posttraumatic Stress Disorder (PTSD) suffer residual symptoms following first-line treatment. Oxidative stress has been implicated in the pathophysiology of PTSD. N-acetylcysteine (NAC) is a precursor of the brain’s primary antioxidant, glutathione, and may diminish oxidative cellular damage. An 8-week pilot study of NAC in veterans with PTSD found that symptoms were significantly reduced in the NAC group compared to placebo. This study aims to confirm these findings with a larger sample in a double-blind, placebo-controlled trial to further explore the efficacy of NAC as an adjunctive therapy in treatment-resistant PTSD.

**Methods:**

A multicentre, randomised, double-blind, placebo-controlled trial for adult patients who still meet criteria for PTSD following first-line treatment. The intervention comprises either NAC as a fixed dose regime of 2.7 g/day (900 mg three times daily) administered orally for 12 weeks, or placebo. Standard care for PTSD will continue in addition, including other pharmacotherapies. Detailed clinical data will be collected at randomisation and weeks 4, 8, 12, 16, and 64 post-randomisation, with self-report measures completed weekly from baseline to 16 weeks and at 64 weeks post-randomisation. Blood-based biomarkers will be collected at baseline and 12 weeks to assess the mechanism of effect. The primary outcome measure will be change in Clinician-Administered PTSD Scale for DSM-5 at 12 weeks compared with baseline. Secondary outcomes will be change in quality of life, depression, anxiety, substance use and craving, and somatic symptoms. With 126 completed participants (63 per arm), the study is powered at 80% to detect a true difference in the primary outcome measure using a two-tailed analysis with alpha = 0.05, beta = 0.2.

**Discussion:**

This is the first multicentre, double blind, randomised, placebo-controlled trial of adjunctive NAC for treatment-resistant PTSD. NAC has an established safety profile, is readily available and easy to administer, and has a favourable tolerability profile, therefore making it an attractive adjunctive therapy. Inclusion of blood analyses to assess potential target engagement biomarkers of oxidative stress and neuroinflammation may help gauge the biological mechanisms of effect of NAC.

**Trial registration:**

ACTRN12618001784202, retrospectively registered 31/10/2018, URL: http://www.anzctr.org.au/Trial/Registration/TrialReview.aspx?id=376004.

## Background

Posttraumatic Stress Disorder (PTSD) is a condition characterized by re-experiencing of trauma, deterioration in cognition and mood, avoidance of triggers and hyper-arousal symptoms after experiencing severely threatening, traumatic events [1]. Large community surveys suggest that most people will experience at least one potentially traumatic event in their lives [2], however in a proportion of individuals, symptoms of psychological distress persist and progress to the development of PTSD. PTSD affects approximately 6% of the population, though rates are considerably higher for certain occupational groups such as emergency service workers and military personnel [3]. It is difficult to treat, with only a quarter of patients achieving full remission with first-line therapy [4].

PTSD is associated with substantial disability as symptoms are usually chronic [5] and accompanied by extensive functional decline, including high rates of unemployment [6], family and relationship difficulties [7], suicidality [8] and reduced quality of life [9]. PTSD is also frequently associated with a variety of comorbidities such as depression, substance abuse and psychosomatic disorders [1]. Recommended first-line treatments of PTSD in Australia are psychological, including trauma-focused psychotherapy, but they suffer from limited tolerability, and many patients discontinue treatment prematurely [10]. Selective-serotonin reuptake inhibitors (SSRIs) are the preferred pharmacological intervention for PTSD, either as alone or in conjunction with psychological therapies [11, 12]. SSRIs have demonstrated only moderate efficacy, however, with the majority of patients failing to achieve remission even when combined with psychotherapy [13, 14]. Those who do not respond to first-line treatment are usually considered treatment-resistant, and by this measure up to 70% of patients with PTSD fall into that category [15].

Several lines of evidence suggest that increased oxidative stress and neuroinflammation are implicated in the pathophysiology of PTSD [16–18]. Oxidative stress occurs when there are excess levels of free radicals, or inadequate antioxidants, potentially leading to cellular damage. Multiple studies in PTSD samples have demonstrated elevated levels of biomarkers of oxidative-stress, including anti-oxidant blood-based enzyme concentrations and altered gene expression [19, 20]. The brain’s primary antioxidant, glutathione, is dysregulated in patients with PTSD, [21] and downregulation of the Glutathione-S-Transferase Mu1 & 2 genes, responsible for encoding enzymes involved in conjugation reactions with glutathione, is considered the most reliable blood-based biomarker for PTSD [22]. Replenishing glutathione could be expected to diminish oxidative cellular damage, and hence potentially ameliorate PTSD symptoms and prevent long-term illness sequelae. However, glutathione is not orally bioavailable. In order to restore glutathione supply, its synthesis must be enhanced, for example by a precursor such as N-acetylcysteine (NAC).

Research indicates that NAC, or more likely its metabolites, can cross the blood-brain barrier [23, 24] and systemic delivery leads to a rise in brain glutathione [25]. While emerging evidence supports the use of NAC in the treatment of other psychiatric disorders [26, 27], this has yet to be thoroughly explored in PTSD. A small pilot study assessing NAC as an adjunct to cognitive-behavioural therapy in a group of US veterans with co-morbid substance use disorders demonstrated significant reductions in self-reported PTSD symptoms, co-morbid depressive symptoms and cravings for substance use compared to the placebo group. In view of these findings and the growing understanding of theoretical foundations of oxidation biology, NAC appears well placed as a potential adjunctive treatment for PTSD. It is well-tolerated [28, 29], low cost and is available without prescription. To date, NAC has yet to be evaluated in a large scale, randomised clinical trial as an adjuvant treatment for PTSD.

### Study objectives

This study aims to investigate the efficacy of adjunctive NAC for patients with treatment-resistant PTSD. It is hypothesised that NAC plus treatment as usual, will be superior to placebo plus treatment as usual in reducing clinician-assessed PTSD symptoms in an adult PTSD sample. It is also hypothesised that adjunctive NAC will result in a reduction in self-reported PTSD, depressive and somatic symptoms, substance use and cravings, and improvement in quality of life. This study will also explore blood-based biomarkers in PTSD to elucidate the mechanisms of action of NAC on PTSD symptoms.

## Methods

### Study design and setting

This study is a multi-site, 12-week, double-blind, randomised, placebo-controlled trial. The trial will be conducted at two tertiary mental-health centres in Australia which provide specialist PTSD treatment services: Austin Health’s public Psychological Trauma Recovery Service (PTRS) and The Melbourne Clinic (TMC) which is a private psychiatric hospital. Both sites acquired ethics approval to allow recruitment of participants from their clinical services and from the general community.

### Patient and public involvement

Patients or the public were not involved in the design, or conduct, or reporting, or dissemination plans of this study.

### Patients

Eligibility criteria are outlined in Table 1. The target population includes individuals aged 18 and older who meet Diagnostic & Statistical Manual of Mental Disorders - Fifth edition (DSM-5) diagnostic criteria for current PTSD despite having undergone a recommended course of treatment. A treatment course is defined as a full course of trauma-focused psychotherapy or a 6-week (minimum) course of pharmacotherapy (SSRI or SNRI). Participants may continue their usual treatments during the study. Participants must have the capacity to consent to the study and to follow its instructions and procedures.

**Table 1 Tab1:** Inclusion and Exclusion Criteria

Inclusion criteria	Exclusion criteria
Age ≥ 18 and able to provide written informed consent	Already taking NAC, selenium or vitamin E History of anaphylactic reaction to NAC
**Current PTSD** Meets criteria for DSM-5 diagnosis of PTSD according to CAPS-5 monthly version	Known or suspected clinically unstable systemic medical disorder History of epilepsy Current asthma Recent gastrointestinal ulcers
Treatment resistant PTSD defined as (a) Minimum 1x trial of an antidepressant (SSRI or SNRI) for minimum 6 weeks without adequate response OR (b) completed a course of trauma-focused psychotherapy	Currently pregnant or breastfeeding Planning to conceive a child during the trial or 3 months following
If currently taking an antidepressant medication • Minimum of 6-weeks if recently initiated • Dose must be stable for minimum 2 weeks	History of psychotic illness

*NAC* N-acetyl cysteine, *PTSD* Posttraumatic Stress Disorder, *DSM-5* Diagnostic & Statistical Manual of Mental Disorders Fifth edition, *CAPS-5* Clinician-Administered PTSD Scale for DSM-5, *SSRI* Selective-serotonin reuptake inhibitor, *SNRI* Serotonin and norepinephrine reuptake inhibitor

### Sample size calculation and recruitment target

The target sample size is 126 participants (63 per arm). For a two-tailed analysis with alpha = 0.05, beta = 0.2, the study is powered at 80% to detect a true difference in CAPS-5 scores between the NAC and placebo groups of 10+/− 20 points. In our pilot trial, effect sizes for PTSD symptoms as well as all secondary measures exceeded this threshold. Using a conservative attrition rate of one-third, we will need to recruit 190 participants to have 126 complete the trial and follow-up.

The study aims to recruit participants referred by their treating clinician or self-referred from the community. A summary of the participant flow through the study is shown in Fig. 1.

**Fig. 1 Fig1:**
[figure not shown]
Trial Flow Diagram. NAC – N-Acetyl Cysteine; RT – Routine treatment; PCL-5 – PTSD Checklist 5

### Screening phase and baseline assessment

Individuals with PTSD who express interest in participating in the study will be contacted by a trial clinician and screened according to the eligibility criteria outlined in Table 1 via a brief telephone interview.

After initial telephone screening, eligible participants will be invited to a face-to-face or videoconference 90-min clinical interview. After obtaining IRB-approved written informed consent, a diagnosis of PTSD will be confirmed through the Clinician-Administered PTSD Scale for DSM-5 (CAPS-5) – monthly version, which is the gold-standard in PTSD assessment. Participants will be excluded if they do not meet diagnostic criteria for current PTSD. If patients are deemed eligible and are enrolled in the study, this interview will constitute part of the baseline assessment.

The baseline assessment will also include data collection via clinician-administered and self-reported questionnaires regarding psychiatric comorbidities, PTSD symptoms, quality of life, substance use and somatic symptoms (see Table 2). Detailed clinical and demographic information will be collected on all participants at the baseline clinical interview. This will include age, gender, marital status, years of formal education, service history, receipt of state benefits, ethnicity, and country of birth.

**Table 2 Tab2:** Primary and secondary outcomes according to time-point

Outcome	Measure	Trial							Post-trial		
		Baseline	W 1–3	W 4	W 5–7	W 8	W 9–11	W 12	W 13–15	W 16	W 64
**Primary Outcome**											
*Trauma history, PTSD diagnosis and symptom severity*	**CAPS-5** (monthly version; 30-item observer rated questionnaire, corresponding to the *DSM-5* diagnosis for PTSD) [30]	X						X		X	X
*PTSD symptom severity*	**CAPS-5** (weekly version)	X		X		X		X		X	
**Secondary Outcomes**											
*Depression & Anxiety*	**HADS** (14 item self-report screening measure of anxiety and depression, designed for use in medical settings) [31]	X		X		X		X		X	X
	**HAM-D** (17 item observer rated scale; evaluates core symptoms of depression) [32]										
*Self-rated PTSD symptoms*	**PCL-5** (20 item self-report measure of PTSD symptoms) [33]	X	X	X	X	X	X	X	X	X	X
*Somatic symptoms*	**PHQ-15** (15 item self-report measure of degree to which one has been bothered by somatic symptoms over the past month) [34]	X		X		X		X		X	X
*Quality of life*	**WHO-QOL BREV** (26 item measure of subjective quality of life) [35]	X		X		X		X		X	X
*Alcohol use*	**AUDIT** (Participant answer ten-items relating to frequency of symptoms and behaviours associated with alcohol misuse) [36]	X		X		X		X		X	X
*Substance craving*	**Visual Analogue Scale** (to assess substance craving over the past week. Participants will rate 5 items using anchors of 0 (“not at all”) to 10 (“extreme” or “all the time”)	X		X		X		X		X	X
*Biomarkers of oxidative stress*	**Optional blood analysis** (IL-6, TNF-alpha, TBARS, MDA, BDNF)	X						X			
**Other Measures**											
*Other psychiatric comorbidities*	**MINI V 5.0** (Semi-structured interview to assess habitual substance use and psychiatric comorbidities, including psychotic disorders) [37]	X									
*Demographic Information*	Questionnaire	X									
*Adverse effects*	Self-report			X		X		X			

Indicates clinical interview

Participants will be provided with a signed copy of their information and consent form which includes written information regarding study protocol, purpose, data handling, participant confidentiality, potential side-effects and their right to withdraw from the study at any time.

### Allocation

Randomisation will take place only once participants have undertaken the baseline assessment and are confirmed eligible for the trial. If all inclusion and exclusion criteria are satisfied, trial participants will be randomised at a 1:1 ratio to the NAC (treatment) or placebo arm. Random block allocation of medication packs will be in a four-to-a-block design, randomly generated by a computer program. Randomisation will be carried out by the clinical trial pharmacy service at the trial site. Allocation will be concealed from participants and all other research staff as the study is double blinded.

A fixed dose regime of 2.7 g/day of NAC will be administered as 900 mg three times daily for 12 weeks. Previous pilot studies have demonstrated this dose is efficacious and well-tolerated [28, 29]. The NAC and placebo are either supplied as effervescent tablets or as capsules. The trial medications will be supplied on a monthly basis (to coincide with clinical interviews) and participants will be instructed to return all packaging to allow capsule counts by the trial monitor and the trial pharmacist. Adherence will be assessed by pill counts of returned medication packs. Participants will also be required to complete a daily pill diary to document treatment compliance. The trial medications will be supplied, and returned containers counted, by the trial pharmacist.

### Blinding

To facilitate the double-blinding process, the trial medications (both NAC and placebo) will be dispensed in identical numbers and tablet forms in sealed containers, and the placebo containers will be specially treated with microgram levels of NAC dust to produce its characteristic smell. Placebo will be manufactured according to European Medicine Agency (EMA) guidelines. We will require research workers to indicate if they have become unblinded so that outcome assessments can be undertaken by blinded assessors in addition to any established treatments for their PTSD.

### Follow-up assessments

Following baseline assessment and enrolment in the trial, participants will be assessed with clinical interviews at weeks 4, 8 and 12 of the trial. Post-trial interviews are conducted at 16 weeks and 64 weeks to assess retention of any treatment effects. At each follow-up assessment, clinician-rated PTSD symptoms, and self-reported PTSD symptoms as well as psychiatric comorbidities, quality of life, substance use and somatic symptoms are assessed (see Table 2). In between follow-up interviews (from Baseline to Week 16), participants will complete weekly self-report questionnaires regarding their PTSD symptoms. Follow-up interviews will take about 60 min to complete; the weekly self-report questionnaire take approximately 5 min.

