### Outcomes

Our primary evaluation of treatment efficacy is the reduction of observer-rated PTSD symptom severity, operationalised as a reduction CAPS-5 severity scores. Secondary objectives include evaluation of NAC to reduce self-reported symptoms of (1) PTSD, (2) depression and anxiety, (3) substance use, (4) craving and (5) somatic symptoms. Evaluation of treatment efficacy will be assessed over the entire trial period. Retention of treatment effects will be assessed at weeks 16 and 64 post-randomisation. The safety and tolerability of the intervention will be evaluated by self-report.

Participants may elect to provide a blood sample at baseline and Week 12 assessments. Blood based biomarkers of oxidative stress will be evaluated as exploratory outcomes. Blood analysis will include measurement of IL-6 (interleukin-6), TNF-alpha (tumour necrosis factor alpha), TBARS (thiobarbituric acid reactive substances), MDA (malondialdehyde) and BDNF (brain-derived neurotrophic factor). Modulation of these blood-based proteins will be correlated with treatment response. Participants will not be fasting prior to the blood collection. BD vacutainer SST II advance tubes (5 mL) will be used to collect the sample and then allowed to rest for 30 min prior to being centrifuged at 1300 g for 15 mins. The supernatant (serum) will be extracted and aliquoted into 2 × 1.8 ml tubes. All samples will be stored at − 80 degrees Celsius until tested.

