### Participant safety and withdrawal

Adverse effects will be assessed each week and reviewed by the study team as well as the Data Safety Monitoring Board, comprising the investigators. Though serious adverse events with NAC are extremely rare, patients will be advised to seek appropriate emergency medical help in such an instance. For less serious events, participants will be advised to contact their treating physician as usual. Participants will be withdrawn from the trial under the following conditions: (i) failure to take the trial medication for seven consecutive days; (ii) cessation of effective contraception or pregnancy; and (iii) withdrawal of consent or emergence of adverse events (as determined by the medical investigators or decision of the participant). All data will be retained in the intention-to-treat analysis.

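### Table 2 schedules the last adverse-effect self-report at week 12, when dosing ends; the safety text gives a different frequency and no end date, and nothing is scheduled at the week-16 interview

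*Protocol article*

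**What the plan says.** The Allocation section describes study drug as "administered as 900 mg three times daily for 12 weeks", so week 12 is the end of dosing. The Outcomes section makes safety a declared evaluation: "The safety and tolerability of the intervention will be evaluated by self-report".

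Three places bear on when that self-report is taken.

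- **Table 2, Other Measures.** The row labelled "Adverse effects" is marked at weeks 4, 8 and 12. The three post-trial columns (weeks 13–15, week 16, week 64) are blank in that row.
- **Participant safety and withdrawal.** This section sets a weekly frequency: "Adverse effects will be assessed each week and reviewed by the study team as well as the Data Safety Monitoring Board, comprising the investigators". No end date is given.
- **Follow-up assessments.** "Post-trial interviews are conducted at 16 weeks and 64 weeks to assess retention of any treatment effects". The content of each follow-up is given as clinician-rated and self-reported PTSD symptoms together with "psychiatric comorbidities, quality of life, substance use and somatic symptoms are assessed (see Table 2"). Between interviews, up to week 16, participants complete a weekly questionnaire on PTSD symptoms.

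**The concern.** The trial keeps in contact with participants after the last dose, but the only schedule that ties adverse-effect collection to visits stops on the day dosing stops. Anything that starts in the following four weeks, including anything that follows stopping the drug, has no scheduled record as an adverse effect. The same holds for the later course of anything still present at week 12.

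The safety text might have settled the matter, but it gives a different frequency and no end. Site staff and the analyst therefore cannot tell from the article which period the safety tables will cover. At stake is the completeness of the tolerability results; the primary efficacy comparison is not affected.

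**Working it through.** The point concerns the visit schedule, so the check sets the passages side by side and counts.

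1. **The plan's own follow-up times.** Week 16 minus week 12 is 4 weeks, and week 64 minus week 12 is 52 weeks. These match the 4 and 52 weeks after trial completion given in the Discussion, so week 12 is the end of treatment throughout.

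2. **Reading Table 2.** The header has two label columns and ten time columns: baseline, weeks 1–3, 4, 5–7, 8, 9–11 and 12 under the trial heading, then weeks 13–15, 16 and 64 under the post-trial heading. The adverse-effects row has the same 12 cells, with marks at weeks 4, 8 and 12.

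3. **Is the row misaligned?** The same reading puts PCL-5 in all ten time columns, and PHQ-15 at baseline and weeks 4, 8, 12, 16 and 64. Both agree with the Follow-up assessments text (weekly PTSD self-report to week 16; interviews at weeks 4, 8, 12, 16 and 64). Misalignment is therefore unlikely.

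4. **Contacts after dosing.** PCL-5 at weeks 13, 14 and 15 gives 3, and the interviews at weeks 16 and 64 give 2, so 3 + 2 = 5 contacts collect outcome scales. Adverse-effect marks in those columns: 0.

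5. **Table 2 against the safety text.** Weekly assessment through week 12 means 12 occasions. Table 2 shows 3, so 12 − 3 = 9 are absent: three each in weeks 1–3, 5–7 and 9–11. If weekly assessment were meant to run to week 16, a further 16 − 12 = 4 occasions (weeks 13 to 16) would be expected, and Table 2 shows none.

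6. **Could the weekly contact carry the adverse-effect question?** In the between-interview columns the only measure marked is PCL-5. The Follow-up assessments section describes the weekly form as covering PTSD symptoms, and the section on standardised medical care mentions one weekly self-report questionnaire. No adverse-effect item is attached to it.

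7. **The list of follow-up content.** It omits adverse effects, but it covers all follow-ups, including weeks 4, 8 and 12, where Table 2 does schedule them. Its silence is therefore weak evidence on its own. The Table 2 row is the evidence that matters.

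**The case against.** The strongest reply is that the safety text has no end date and the only weekly contact described runs to week 16, so weekly adverse-effect collection to week 16 may be what is meant. If the safety text is right, Table 2 already leaves out nine on-treatment occasions, and its blanks cannot prove that nothing happens afterwards. This stands in part. A reader might infer from Table 2 that collection after the last dose is definitely nil; the documents support only an unresolved conflict, in which no passage schedules collection after week 12.

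A second reply is that an article condenses a fuller protocol. That is right for following events to resolution, serious events at week 64 and contact with early stoppers, and none of these is raised here. It does not cover the Table 2 row: the article prints a complete schedule with post-trial columns and fills them for the outcome scales but not for adverse effects.

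Third, weeks 16 and 64 are not blind to harm. PHQ-15, HADS and CAPS-5 are collected then, and worsening in one arm could show. This also stands, although these scales record no event, onset or seriousness.

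Two further readings are tempting and unsupported.

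- A reader might take the exclusion "Planning to conceive a child during the trial or 3 months following" as an admission that drug risk outlasts dosing. The article gives no reason for the criterion, and it reads equally well as routine precaution.
- A reader might say that following benefit for 52 weeks and harm for none biases the trial towards NAC. No benefit-risk statement at week 16 or 64 is announced, and the schedule is the same in both arms.

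**Conclusion.** The point holds as a gap in the schedule combined with an internal conflict. The last scheduled adverse-effect self-report coincides with the end of dosing; none of the three post-trial columns has an entry; and the safety text contradicts Table 2 on frequency without saying when collection ends. Effects starting after week 12, or open at that visit, are not scheduled to be recorded as adverse effects, although some may appear incidentally in the outcome scales.

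The size is five post-dosing contacts with no adverse-effect entry, the nearest being the week-16 interview four weeks after dosing ends. It cannot be turned into a number of participants: the documents give no rate of delayed or post-cessation effects, and the safety section describes serious events with NAC as extremely rare.

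The conclusion assumes that the Table 2 row is read correctly and that no other safety schedule applies. The full protocol is not shown and could contain one. The gap does not threaten the primary result, but it is worth correcting because safety is a declared evaluation and the correction is cheap.

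**What to change.** - Reconcile the adverse-effects row of Table 2 with the weekly frequency in the section on participant safety, so that one schedule applies.
- State when adverse-effect collection ends.
- Add the existing adverse-effect self-report to the week-16 column of Table 2, asking about onset since week 12 and the status of anything open at week 12. Report it by arm.

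The interview already takes place and lasts about 60 minutes, so no new visit is needed. The cost is a slightly longer week-16 interview and one extra table. Sample size, treatment and the primary analysis are unchanged.
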